## Abstract

**Background:**

Severe traumatic injury and haemorrhagic shock are frequently associated with disruptions of coagulation function (such as trauma-induced coagulopathy TIC) and activation of inflammatory cascades. These pathologies may be exacerbated by current standard of care resuscitation protocols. Observational studies suggest early administration of plasma to severely-injured haemorrhaging patients may correct TIC, minimise inflammation, and improve survival. The proposed randomised clinical trial will evaluate the clinical effectiveness of pre-hospital plasma administration compared with standard- of-care crystalloid resuscitation in severely-injured patients with major traumatic haemorrhage.

**Methods/design:**

This is a prospective, randomized, open-label, non-blinded trial to determine the effect of pre-hospital administration of thawed plasma (TP) on mortality, morbidity, transfusion requirements, coagulation, and inflammatory response in severely-injured bleeding trauma patients. Two hundred and ten eligible adult trauma patients will be randomised to receive either two units of plasma, to be administered in-field, *vs* standard of care normal saline (NS). Main analyses will compare subjects allocated to TP to those allocated to NS, on an intention-to-treat basis. Primary outcome measure is all-cause 30-day mortality. Secondary outcome measures include coagulation and lipidomic/pro-inflammatory marker responses, volume of resuscitation fluids (crystalloid, colloid) and blood products administered, and major hospital outcomes (e.g. incidence of MSOF, length of ICU stay, length of hospital stay).

**Discussion:**

This study is part of a US Department of Defense (DoD)-funded multi-institutional investigation, conducted independently of, but in parallel with, the University of Pittsburgh and University of Denver. Demonstration of significant reductions in mortality and coagulopathic/inflammatory-related morbidities as a result of pre-hospital plasma administration would be of considerable clinical importance for the management of haemorrhagic shock in both civilian and military populations.

**Trial registration:**

ClinicalTrials.gov: NCT02303964 on 28 November 2014

## Background

Following severe traumatic injury, the immediate care priorities are control of bleeding and correction of the hypovolemia and tissue hypoperfusion that result from excessive blood loss and tissue injury. Massive hemorrhage (MH) requires surgical intervention for definitive hemostasis. However, trauma-related hemorrhagic shock is also a disease of ischemic cellular injury and death, resulting from coagulation disruption and inflammatory precursor activation [7, 15, 23]. Approximately 25 % of severely injured patients present with severely abnormal coagulation changes occurring within very few hours of injury [22]. This so-called trauma-induced coagulopathy (TIC) is associated with 4-fold increase in mortality, increased rates of late death from sepsis and multiple organ failure (MOF), and worsened outcomes from traumatic brain injury (TBI) [4, 5, 13]. Ischemic cellular injury resulting from uncorrected, persistent, and systemic hypoperfusion eventually leads to systemic inflammatory response syndrome and irreversible multi-system organ failure (MSOF). MSOF is a major cause of late mortality and morbidity following severe trauma, with a mortality rate of 50 % to 80 % [20].

To minimize irreversible cell damage and death, it follows that recognition of MH should occur as soon as possible after injury and as far upstream as possible from initiation of coagulopathy/inflammatory cascades. Unfortunately early recognition may not be easily achieved, especially if bleeding is primarily internal. In practice, the extent of hemorrhage and shock during the initial assessment stage is based on vital signs, primarily blood pressure, pulse rate, palpable radial pulses, and mentation [1]. However these are extremely variable, non-specific, and very poor indicators of perfusion status [29]. Therefore choice of first-line resuscitation fluids will be essential for preempting some of the negative outcomes of unrecognized MH and shock.

There is increased interest in reviving prehospital use of plasma transfusions for severely injured hemorrhaging patients, especially if time to definitive care is long. Observational data suggest improved 6-hr outcomes but no overall survival advantage with prehospital blood product administration [17]. Better patient 30-d survival was associated with earlier (<4 hr) in-hospital administration of relatively high ratios of plasma to packed red blood cells (pRBC) in both civilian [10, 18] and military [3] trauma populations; meta-analysis supports early use of plasma but does not conclude that there are additional survival benefits of 1:1 over 1:2 plasma:pRBC transfusion ratios [2] In contrast, plasma transfusions have been associated with increased morbidity and mortality in other studies of trauma [21] and non-MH patients [24, 26, 27]. However, interpretations of data from these studies may be confounded by lack of standardization in hospital resuscitation protocols, changes in transfusion practice over the past decade, confounding-by-indication bias [19] and survivor bias [16].

At present there are no data either from systematic reviews [11] or from completed, prospective, randomized controlled clinical trials [19] to assess the efficacy of plasma transfusion alone. Further, there are no rigorous definitions of how early infusion must occur relative to injury in order to demonstrate benefit. This study will be one of three prehospital trials conducted in parallel that explicitly examines the effect of prehospital plasma transfusion on mortality and morbidity in civilian trauma patient populations.

## Methods/Design

### Study design

This study is a prospective, open-label, non-blinded, randomized clinical trial to quantify the effects of early prehospital administration of plasma on death, coagulation function, transfusion requirements, and other relevant clinical outcomes for seriously-injured trauma patients with massive bleeding. Trial flow per the Consolidated Standards of Reporting Trials (CONSORT) guidelines [25] is shown in Fig. 1.

**Fig. 1 Fig1:**
[figure not shown]
Consolidated Standards of Reporting Trials (CONSORT) flow diagram of phase progress for the Virginia Commonwealth University (VCU) plasma trial (PUPTH), a parallel randomized trial of prehospital administration of plasma vs standard-of-care normal saline in a trauma population. *ED* Emergency Department

### Ethical oversight

The study was approved by the Virginia Commonwealth University Institutional Review Board (VCU-IRB Protocol Record HM14813), Food and Drug Administration (FDA) (IND no. 15910); and the US Department of Defense (HRPO Log Number A-17160). The study was listed with the Clinical Trials register on 28 November 2014 (ClinicalTrials.gov number NCT02303964).

### Study population

The study population consists of adult, physiologically unstable, polytrauma patients transported to Virginia Commonwealth University Medical Center (VCUMC), a Level I trauma center. The catchment area is Henrico County and City of Richmond, Virginia. Henrico Fire EMS system (HFD) serves a population of 325,000 with over 30,000 transports per year; the city of Richmond EMS system (Richmond Ambulance Authority, RAA) serves a metro area of 222,000 with over 27,000 transports per year.

#### Inclusion criteria

Patients eligible for this study include all adult (≥18 years) patients of either sex, with blunt and/or penetrating trauma with multi-system injuries and unstable vital signs (systolic blood pressure (SBP) ≤70 mmHg, or SBP 70–90 mmHg with heart rate (HR) ≥108 beats per minute (bpm)), indicative of severe ongoing hemorrhage.

Exclusion criteria are: (1) presence of an opt-out wrist band, wallet card, Medical Alert jewelry, bracelet, or similar identifier to indicate Jehovah’s Witness or similar patient group objecting to transfusion of blood and/or blood products; (2) refusal of consent by patient or legally appointed representative (LAR); (3) language barrier (non-English or non-Spanish speaking); (4) not expected to survive transport to VCUMC (based on extreme severity of injuries, on-scene cardiac arrest, and/or cardiopulmonary resuscitation (CPR) prior to randomization); (5) documented do not resuscitate (DNR) order; (6) isolated penetrating head trauma; (7) burns to >20 % of the body surface; (8) pregnancy; (9) prisoner; (10) if patient transport has proceeded before arrival at the scene by the emergency medical services (EMS) supervisor with plasma, and (11) failure of the EMS to obtain intravenous (IV) access.

#### Patient drop-out

Patients may refuse consent and leave the study at any time for any reason. Subjects can be withdrawn from the study emergently by the attending study physician if they develop signs and symptoms of acute transfusion reaction.

### Interventions and controls

Patients will be randomized prior to arrival at the Emergency Department (ED) to receive either thawed fresh-frozen plasma (TP) or standard-of-care normal saline (NS) during prehospital transport. Patients randomized to the TP arm will receive up to two units of pre-thawed A+ plasma. The control intervention is standard-of-care NS administered IV/intra-osseous (IO) per prehospital (ODEMSA) protocol to maintain SBP at 90–100 mmHg.

The VCUMC Blood Bank will provide plasma to EMS supervisors. Use of low-titer anti-B (<1:100) A+, rather than AB (universal donor), plasma is justified on the grounds of the scarcity of AB plasma, and because of the extremely small risk of hemolytic reaction associated with administering A+ to patients who are not blood group compatible (incidence 0.1–1 %) [9]. TP will be maintained in dedicated refrigeration units in the EMS supervisor vehicle; unused TP will be exchanged within 24 hr to the VCUMC Blood Bank.

### Randomization

Eligible patients will be randomly assigned to receive either TP or NS prior to ED arrival. Randomization codes will be generated using complete randomization; code sequence is secured by trial statisticians, and held at the VCUMC Transfer Call Center in sealed opaque envelopes. Patients will be screened for eligibility by on-scene prehospital providers. Endorsement for plasma administration will be given by the study physician on call. At this point the patient is considered enrolled into the study. Transfer Centre personnel will then open the next envelope in sequence and advise EMS as to patient allocation.

### Study outcomes

The primary outcome of this study will be all-cause 30-day mortality. Secondary outcomes are: (1) hemodynamics (specifically SBP, mean arterial pressure (MAP), and HR); (2) cumulative volume of resuscitation fluids and blood products utilized at 8 and 24 hr from injury (volumes of crystalloid and/or colloid, units of red blood cells, units of plasma, doses of platelets, doses of cryoprecipitate); (3) hematology (hemoglobin (Hb) and hematocrit (Hct)) and blood biochemistry (pH, lactate, base deficit, and bicarbonate); (4) coagulation function (thromboelastography (TEG), fibrinogen, FV, FVIII, prothrombin time (PT), activated partial prothrombin time (aPTT), von Willebrand’s factor, D-dimer, PFA-100, and platelet count); (5) lipidomic profile (arachidonic acid, eicosanoid, and prostacyclin expression); (6) hospital outcomes on days 7 and 30 (rates of MSOF, rates of acute renal failure (ARF), number of surgeries, number of infections, duration of mechanical ventilation, length of ICU stay, and length of hospital stay).

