### Timelines

Follow up of patients enrolled in the trial ends at death or 30 days post-randomization, whichever occurs first. Patients discharged before 30 days will be followed up via telephone by designated study personnel. Blood samples for coagulation function and lipidomic profiling will be collected from each patient at four pre-specified time points: prehospital (close to point of injury, and before prehospital resuscitation), in the ED (approximately 30 min from hospital admission), and at 8 and 24 hr from admission.

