### Post-randomization treatment

All clinically indicated treatments (including blood product and fluid administration) will be given as appropriate per attending physician discretion. Standard of care for polytrauma patients with MH includes administration of TP plus blood products and/or crystalloid and colloid shortly after reaching VCUMC ED, unless otherwise indicated. In addition to administration of trial resuscitation treatments (TP or NS), trial-specific interventions will include blood sampling for coagulation function and lipidomic determinations; Approximately 20 mL of blood will be obtained from each patient at four time points.

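### Plasma and crystalloid volumes counted from injury include the randomised fluid, so the plasma difference, and probably the crystalloid difference, cannot be read as an effect on transfusion requirements

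*Protocol article*

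**What the plan says.** The protocol article (Study outcomes) defines secondary outcome (2) as "cumulative volume of resuscitation fluids and blood products utilized at 8 and 24 hr from injury" and lists the components as "volumes of crystalloid and/or colloid, units of red blood cells, units of plasma, doses of platelets, doses of cryoprecipitate". It thus fixes both the time origin and the products counted.

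Interventions and controls describes the randomised fluid. For the experimental arm: "Patients randomized to the TP arm will receive up to two units of pre-thawed A+ plasma". For control: "The control intervention is standard-of-care NS administered IV/intra-osseous (IO) per prehospital (ODEMSA) protocol to maintain SBP at 90–100 mmHg". Both are given before Emergency Department (ED) arrival; the control fluid, for example, is "standard-of-care normal saline (NS) during prehospital transport".

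Study design states the aim as to "quantify the effects of early prehospital administration of plasma on death, coagulation function, transfusion requirements", and the Abstract also names transfusion requirements. No section of the article as shown excludes the study fluid from outcome (2) or separates it from other fluid.

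Two further statements bear on size. Post-randomization treatment says "Standard of care for polytrauma patients with MH includes administration of TP plus blood products and/or crystalloid and colloid shortly after reaching VCUMC ED", so both arms may receive plasma and crystalloid in hospital. The Discussion accepts that some TP patients will not have received both units by hospital arrival.

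**The concern.** For two named components, the outcome counts the treatment as part of the response to treatment. The plasma comparison can then mislead in two ways:

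- If prehospital plasma does nothing to later need, the TP arm is still expected to show more plasma used.
- If prehospital plasma does reduce later plasma use, the study units cancel the reduction in the total, partly or wholly.

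A reader who takes the plasma line of outcome (2) as the answer to the stated aim on transfusion requirements could draw the wrong conclusion in either case. The primary outcome, 30-day mortality, is not touched.

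**Working it through.** **Inputs from the article.** Study plasma per TP patient: 0 to 2 units (Interventions and controls). Patients per arm: 105 (Estimated event rate and sample size calculations). Analysis by allocated arm (Data analyses).

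**Inputs assumed.** The article gives no mean or SD for plasma use. I take a common SD of 2 to 10 units, a mean delivered study dose of 1 to 2 units, two-sided alpha 0.05 and a normal approximation.

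**The plan's own figure.** The only calculation that can be reproduced is the mortality sample size. For 24% against 9.6%, with 80% power, two-sided alpha 0.05 (alpha is not stated), pooled variance and no continuity correction, n = 105 per arm, with power 80.1%. This matches. The present point uses only the 105.

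**Step 1: what the arm difference contains.** Let d be the mean study plasma dose in the TP arm, and r the mean reduction in other plasma caused by treatment. Then

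expected difference in total plasma (TP − NS) = d − r, with 0 < d ≤ 2.

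- No later effect (r = 0): the difference is d, which is positive.
- Partial effect, e.g. d = 1.5 and r = 1: the total shows +0.5 units although other plasma use fell by 1.
- Full offset (r = d): the total shows 0, although other plasma use fell by the whole study dose.

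**Step 2: chance of a significant plasma excess when r = 0.**

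SE = SD × √(2/105). SD 4 gives 0.552; SD 6 gives 0.828.

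z = d/SE, and the chance is about Φ(z − 1.96).

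- SD 4: d = 1.5 gives z = 2.72, chance 0.78; d = 2 gives z = 3.62, chance 0.95.
- SD 6: d = 1.5 gives z = 1.81, chance 0.44; d = 2 gives z = 2.42, chance 0.68.

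Wider range by the same formula:

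| Assumed SD (units) | d = 1 | d = 1.5 | d = 2 |
|---|---|---|---|
| 2 | 0.952 | 1.000 | 1.000 |
| 4 | 0.441 | 0.776 | 0.952 |
| 6 | 0.226 | 0.441 | 0.676 |
| 8 | 0.146 | 0.274 | 0.441 |
| 10 | 0.108 | 0.191 | 0.305 |

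With a shift of zero, the chance is 0.025 in this direction, or 5% over both. The d = 1 column also describes a 2-unit dose that is half offset in hospital.

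**Step 3: crystalloid.** Prehospital saline in the NS arm is counted in the same way. No size can be given: saline is titrated to blood pressure with no fixed volume, and the article does not say whether TP patients also receive prehospital saline. A built-in difference is likely but not established.

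**Step 4: other components.** Red cells, platelets, cryoprecipitate and colloid are not study fluids in either arm, so Step 1 does not apply to them.

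**The case against.** The strongest reply is that total use from injury, analysed by allocated arm, is a legitimate quantity. It asks whether prehospital plasma changes net product use, and a later saving of two units against two study units is correctly shown as no net change. The outcome itself is worded in terms of use; transfusion requirements appears only in the general aims. This stands as a defence of keeping the total. It does not support reading the plasma total as a measure of later need, which is what the stated aim invites.

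A second reply is that counting only later fluid has its own artefact. If patients need a roughly fixed amount of plasma, those given some early will need less later by simple substitution. Starting the count at ED arrival would also condition on surviving to the ED. Both points stand and shape the fix.

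A third is that an article may leave the tabulation of study product to a full protocol or SAP. That is fair for tabulation. However, the article itself fixes the time origin and components, and on those terms study fluid is counted.

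A reader might go further and infer that a significant difference is certain by design, or that the whole outcome is uninformative. The documents support neither. Delivery is partial, in-hospital use may offset it, no SD is given, and four of the listed product types are unaffected. Fluid given before randomisation also lies inside the window, but it is balanced in expectation and adds noise rather than bias.

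**Conclusion.** The point holds for plasma and probably for crystalloid. As defined, the plasma difference is the mean study dose minus any later saving, and the two parts cannot be separated from the total. With no later effect, the expected excess in the TP arm is above 0 and at most 2 units.

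How often that would reach significance rests on an SD and a delivered dose that the article does not give: about 44–95% for SD 4–6 and a shift of 1.5–2 units, and from about 11% to nearly 100% over the whole table. The existence of the shift does not depend on these assumptions; its statistical visibility does.

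This affects the interpretation of part of one secondary outcome and is worth correcting. A minor related point is that volumes run from injury, while the later blood samples are taken "and at 8 and 24 hr from admission". A reader might infer that this invalidates a joint analysis, but the article describes no analysis that pairs them.

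**What to change.** 1. Keep the cumulative totals from injury, labelled as total product exposure.
2. Report study plasma and study saline separately, by arm.
3. Add non-study plasma and non-study crystalloid given after randomisation, at 8 and 24 hr, as the measure of later requirement. Include all randomised patients, not only those who reach the ED. State how any prehospital saline in the TP arm is classed, so that the two arms are handled on a stated rule.
4. Read the new measure alongside the total, because substitution alone can lower it.
5. State clearly which clock applies to volumes and which to blood samples.

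The cost is outcome wording and a little extra tabulation, with no change to treatment or sample size. It depends on study fluid being separable from other fluid in the records. The article does not say that it is; Protocol adherence shows only that receipt of the appropriate fluid is checked for each patient. This should be confirmed before the definition is changed.

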### Other data

Patient demographics (age, sex, height, weight, past medical history, comorbidities, medications), mechanism of injury, injury severity assessments—Glasgow coma score (GCS), injury severity score (ISS), sequential organ failure assessment (SOFA), and acute physiology and chronic health evaluation (APACHE IV), routine vital signs and laboratory data, hospital-care-mandated medications and interventions (e.g., intubation, mechanical ventilation, chest thoracotomy, and needle decompression, etc.)—will be collected from individual medical records as they become available after patient admission.

### Timelines

Follow up of patients enrolled in the trial ends at death or 30 days post-randomization, whichever occurs first. Patients discharged before 30 days will be followed up via telephone by designated study personnel. Blood samples for coagulation function and lipidomic profiling will be collected from each patient at four pre-specified time points: prehospital (close to point of injury, and before prehospital resuscitation), in the ED (approximately 30 min from hospital admission), and at 8 and 24 hr from admission.

### Estimated event rate and sample size calculations

VCU Trauma Center registry data suggest that 30-day mortality under the standard-of-care protocol is between 16.4 % and 29.2 %; this is similar to the estimated 26 % mortality for the control arm of the Resuscitation Outcomes Consortium (ROC) prehospital hypertonic saline trial [6]. Assuming 24 % mortality in the control group, a sample size of 105 per arm will achieve 80 % power to detect a clinically significant reduction in mortality of 60 % (9.6 % mortality) in the plasma group [12].

### Disclosure, consent, and confidentiality protection

#### Community consultation and public disclosure procedures

Pre-trial public disclosure (required by 21 CFR 50.24) was completed in 2013–2014. Information was disseminated by community meetings, web-based and social media outlets, paid advertisements, and media news releases to TV, radio, and newspapers. Public disclosure included a summary of investigational plans, background information about the study, a synopsis of the protocol and study design, risks and benefits of plasma versus the standard crystalloid fluid, subject selection, exception from informed consent requirements, procedures for contacting LARs, and procedures for declining participation in the study. Following study termination, findings of the clinical trial will be disseminated to the community by media news releases, the trial website (http://www.cctr.vcu.edu/news/feature/plasma.html), and relevant patient organizations.

